## Oversight and monitoring

### Composition of the coordinating center and trial steering committee {5d}

A trial steering committee will be established to manage, recruit, and ensure that the trial is conducted properly. The team consists of project leaders, researchers, and funders. A monthly meeting will be held in the trial preparation phase and a quarterly meeting in the trial conduct phase, and a written research report will be prepared to report the research progress and problems encountered. In addition, the School of Nursing of Chengdu Medical College and the Ethics Committee of the First Affiliated Hospital of Chengdu Medical College will supervise the study.

### Composition of data monitoring committee, its role and reporting structure {21a}

This is a low-risk intervention and Ethics Committee of the First Affiliated Hospital of Chengdu Medical College does not require one.

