## Assignment of interventions: blinding

### Who will be blinded {17a}

We do not blind the evaluators of the result scale and physical examination but only group them after baseline data collection to avoid the impact of subjective bias on baseline data. In the subsequent result evaluation, the evaluators of the scale and physical examination are not blinded, only the laboratory testers of HbA_1c_ are blinded, and the data analysis personnel are not blinded either.

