### Interim analyses {21b}

Interim analyses will be performed, and we will stop the trial based on interim data analysis, namely if clearly one treatment is better than the other.

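### An efficacy stop is planned, a monitoring committee is declined on low-risk grounds, and no independent body is named to receive the interim comparison

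*Protocol article*

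**What the plan says.** All references are to the protocol article.

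- **Interim analyses {21b}:** "we will stop the trial based on interim data analysis, namely if clearly one treatment is better than the other". This is a comparative efficacy decision. The section does not say who receives the comparison.
- **Data monitoring committee {21a}:** none, because "This is a low-risk intervention and Ethics Committee of the First Affiliated Hospital of Chengdu Medical College does not require one".
- **Steering committee {5d}:** "A trial steering committee will be established to manage, recruit, and ensure that the trial is conducted properly". On membership: "The team consists of project leaders, researchers, and funders". On its output: "a written research report will be prepared to report the research progress and problems encountered".
- **Outside oversight {5d}:** besides the School of Nursing, "the Ethics Committee of the First Affiliated Hospital of Chengdu Medical College will supervise the study". Neither body is given interim data or a part in stopping.
- **Blinding {17a}:** only the HbA1c laboratory testers are blinded. Evaluators of scales and physical examination are not, and "the data analysis personnel are not blinded either".
- **Confidentiality {27}:** access to data is limited to researchers and project leaders.
- **Implementation {16c}:** researchers recruit, with help from clinic doctors and nurses.

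**The concern.** The two adjoining sections do not fit together. The reason given for having no committee concerns participant safety. The need for an independent reader comes from something else: a plan to compare the arms during the trial and to stop if one is ahead. A low-risk intervention does not remove that need.

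Two things are at stake. First, the decision to stop would rest with the people running the trial, with no independent check. Second, if the trial continues after a look, those people know the direction of the result. Being open label is not the same thing: knowing a participant's arm does not tell anyone which arm is winning. That knowledge can affect how hard visits are pursued, the concomitant care that {11d} allows to change, and how open-label outcomes are taken.

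The missing stopping boundary in {21b} is a separate matter. A well-chosen boundary would still leave the trial team reading the comparison.

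**Working it through.** The plan states no figure on this point, so the check is a reading of the sections together, followed by an illustration of exposure.

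**Step 1. Is a between-arm look committed to?** Yes. {21b} states that "Interim analyses will be performed, and we will stop the trial based on interim data analysis", and its criterion is relative benefit.

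**Step 2. Could any body named in the article be the independent reader?**

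| Body or role | What the article gives it | Independent reader of interim data? |
|---|---|---|
| Data monitoring committee {21a} | Declined | No |
| Steering committee {5d} | Management and recruitment; report on progress and problems | No; it includes project leaders and researchers |
| Ethics committee, School of Nursing {5d} | General supervision | Not assigned |
| Analysts {17a} | Unblinded | Not stated to be outside the team |
| Trial review {23} | Done by two participating researchers | No |
| Holders of data access {27} | Researchers and project leaders | No |

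The comparison therefore stays with the trial team as the article is written.

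**Step 3. Could a look fall during recruitment and follow-up?** The inputs are 264 participants and 20% loss (Sample size {14}), start in October 2021 and recruitment to the end of 2023 (Trials status), and 6 months of follow-up. October 2021 to December 2023 is 3 + 12 + 12 = 27 months.

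Assumptions, none of them in the documents: even accrual, a single look, and no dropout except in the last column. For a look when a share s has finished:

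- month of look = 27s + 6
- enrolled by then = 264 × month / 27
- in follow-up = enrolled − 264s
- still to finish = 264 × (1 − s); after loss, multiply by 0.8

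| s | Month | Enrolled | Still to enrol | In follow-up | Still to finish | After 20% loss |
|---|---|---|---|---|---|---|
| 0.25 | 12.75 | 125 | 139 | 59 | 198 | 158 |
| 0.50 | 19.5 | 191 | 73 | 59 | 132 | 106 |
| 0.75 | 26.25 | 257 | 7 | 59 | 66 | 53 |

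Under these assumptions, each of the three looks falls before recruitment closes. The counts show how many participants could be affected. They do not measure bias.

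**Step 4. Which outcomes are protected?** HbA1c is measured at one external laboratory ({12}) by blinded testers ({17a}), so knowledge of the leading arm should not alter the assay. It can still act on retention effort and concomitant care. Blood pressure, body mass index and reported monitoring frequency have no blinded measurer.

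**The case against.** **The article does not say who receives the interim results, and it is a condensed document.** This is fair as far as it goes: the supportable statement is that the article names no independent recipient. But {21a} does not merely omit a committee. It declines one and gives a reason that does not address the efficacy stop, and {27} says who may see data. That is a conflict in what is stated.

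**The primary outcome is well protected.** This largely stands for measurement. The envelopes described under {16a} and {16b} also limit any steering of assignment by recruiters. Neither protects the stop decision, retention effort, concomitant care or the open-label outcomes.

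**Stronger readings that a reader might infer:**

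- *Funders would read the interim results.* They sit on the steering committee, but its report covers progress and problems, and {27} does not list them as having access. What can be said is that nothing states they are kept from the results.
- *The deciders have a stake in the outcome.* The article as shown describes no such interest.
- *The same individuals recruit, train App users and collect every outcome except HbA1c.* The article does not say so. Clinic staff assist recruitment, and participants complete an online questionnaire themselves ({19}), which weakens assessor influence on the scales.
- *Seven of the eight outcomes are compromised by a look.* Seven lack a blinded measurer whether or not there is a look, and satisfaction is collected only in the two App arms. The count does not show what a look would add.

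**Conclusion.** The point holds as an unreconciled conflict between {21a} and {21b}. An efficacy stop is planned, the reason for having no committee does not address it, and no independent body is named to receive the comparison. As written, the unblinded trial team would see which arm is ahead and decide.

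The resulting bias cannot be calculated, because the article gives neither the number nor the timing of looks. On the stated assumptions, the participants still to finish after one look range from 198 to 66, or from 158 to 53 after the planned loss.

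This should be corrected, but it is not fatal. The blinded laboratory limits measurement bias in the primary outcome; the main exposure is the stop decision, conduct after a look, and the open-label secondary outcomes. The conclusion rests on the article alone and would change if the full protocol assigned the interim comparison to an independent reader.

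**What to change.** Reconcile {21a} and {21b}. Delete the comparative efficacy interim analysis and the efficacy stop from {21b}. Keep only arm-pooled monitoring of recruitment, data completeness and hypoglycaemia. The reason given in {21a} then fits the monitoring that remains.

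The cost is the option to stop early for benefit, plus an amendment. The trial is already under way, and {25} requires ethics committee approval for important modifications, so this is more than an edit of wording.

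If a look is kept, state that a body independent of the trial team receives it and returns only a decision to continue or to stop. State also that no arm-level result reaches anyone who recruits, follows up or assesses participants before database lock, and say explicitly whether funders are excluded. This costs more, since someone outside the team must prepare the comparison. If the ethics committee is to be that body, its remit must say so: at present it has general supervision only, with no stated statistical role, and it belongs to the hospital whose nurses sent out recruitment notices ({15}).

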### Adverse event reporting and harms {22}

The adverse events in this study refer to hypoglycemia and will be registered at 3rd month and 6th month after the intervention. And the participants inform the doctor of the number of hypoglycemia times during outpatient visits.

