**Assessments:**				
chronic complications related to diabete		**X**		**X**
acute complications related to diabetes		**X**		**X**
diabetes treatments		**X**		**X**
DKN, HBQ, 2-DSCS		**X**		**X**
satisfaction with the smartphone application				**X**
height, weight, blood pressure and HbA_1c_		**X**	**X**	**X**
frequency of blood glucose monitoring			**X**	**X**

Chronic complications related to diabetes: hypertension, cardiovascular disease, cerebrovascular disease, peripheral vascular disease, kidney disease, peripheral neuropathy, eye disease and diabetic foot; acute complications related to diabetes: hypoglycemia and lactic acidosis or ketoacidosis; diabetes treatments: non-drug therapy, oral hypoglycemic drugs, and insulin therapy

*DKN* Diabetes Knowledge Scale, *HBQ* Health Belief Questionnaire, *2-DSCS* Type 2 Diabetes Self-management Behavior Scale, *user satisfaction with Dnurse application*, custom-made questionnaire to assess user satisfaction with Dnurse application, HbA_1c_ Glycosylated hemoglobin

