## Data collection and management

### Plans for assessment and collection of outcomes {18a}

All participants will complete baseline assessments and complete follow-up at the 3rd and 6th month after the intervention.

At baseline, demographic data will be collected on age, sex, ethnicity, educational level, marital status, employment status, current residence, and method of paying for medical expenses. Data will be collected on the following clinical variables: chronic complications related to diabetes, such as hypertension, cardiovascular disease, cerebrovascular disease, peripheral vascular disease, kidney disease, peripheral neuropathy, eye disease and diabetic foot. Any chronic complications of diabetes that arise during the study will be recorded at the 6th month. Similarly, data on acute complications related to diabetes will be collected at baseline, such as hypoglycemia and lactic acidosis or ketoacidosis; and current diabetes treatments, including non-drug therapy, oral hypoglycemic drugs, and insulin therapy. Any acute complications of diabetes that arise during the study will be recorded at the 6th month.

At baseline and again at the 6th month, all participants will be asked to fill out three questionnaires. In addition, the App and the App + Reminder groups will fill out a fourth questionnaire at 6th month, which assesses their satisfaction with the smartphone application and glucose meter (Table 2). At baseline and again at the 3rd and 6th month, data will be collected on height, weight, blood pressure and HbA_1c_. At the 3rd and 6th month, all participants will be asked about their frequency of blood glucose monitoring.

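### The harms section registers hypoglycaemia at months 3 and 6, but Table 1 and {18a} schedule acute complications, including hypoglycaemia, only at baseline and month 6, and {22} does not count the ketoacidosis and lactic acidosis collected with it as adverse events

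*Protocol article*

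**What the plan says.** Three places in the protocol article bear on this.

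- **Adverse event reporting and harms {22}.** The definition and timing are given in one sentence: "The adverse events in this study refer to hypoglycemia", and these "will be registered at 3rd month and 6th month after the intervention". Ascertainment is by self-report: "the participants inform the doctor of the number of hypoglycemia times during outpatient visits".
- **Table 1.** The footnote places hypoglycaemia in a wider class: "acute complications related to diabetes: hypoglycemia and lactic acidosis or ketoacidosis". The row for that class is marked at 0 and 6 months, and its 3-month cell is empty. The table has no separate row for adverse events.
- **Plans for assessment and collection of outcomes {18a}.** At entry, "data on acute complications related to diabetes will be collected at baseline, such as hypoglycemia and lactic acidosis or ketoacidosis". For the period on study, "Any acute complications of diabetes that arise during the study will be recorded at the 6th month". The items {18a} lists for month 3 are height, weight, blood pressure, HbA1c and monitoring frequency. Hypoglycaemia is not among them.

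Three other sections set the context. {20c} fills a missing month-6 value with the month-3 value. {14} allows for 20% loss to follow-up. {23} includes adverse events among the items that the trial review examines.

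**The concern.** The event that {22} names as the trial's adverse event has two collection schedules. Site staff normally work from the schedule of assessments, and here that schedule has no month-3 entry for the event. Following it has two consequences.

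First, the number of hypoglycaemic episodes would be recalled once over six months instead of over two three-month periods. The count is self-reported and the trial is open label, so a longer recall period weakens the comparison between arms.

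Second, a participant who attends month 3 and then drops out would have an HbA1c value that counts at month 6 by carry-forward, but no scheduled on-study harms record. That person would contribute to the efficacy comparison and not to the harms comparison.

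The definition raises a separate point. "The adverse events in this study refer to hypoglycemia" leaves out lactic acidosis and ketoacidosis, which the trial already collects under the same heading. As worded, they fall outside adverse-event registration and outside the adverse-event part of the review in {23}. The trial has no data monitoring committee ({21a}), so that review carries more weight.

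**Working it through.** No figure in the article underlies the timing conflict, so the check is mainly a comparison of text.

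**Step 1: visits at which each event is scheduled**

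| Source | Event | Baseline | Month 3 | Month 6 |
|---|---|---|---|---|
| {22} | Hypoglycaemia | not stated | yes | yes |
| Table 1 | Acute complications (hypoglycaemia, lactic acidosis or ketoacidosis) | yes | empty | yes |
| {18a} | Acute complications (same events) | yes | not listed | yes |

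Table 1 and {18a} agree, so the conflict is {22} against those two. The baseline entry is not part of it, since it records history before the intervention. The difference is at month 3.

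**Step 2: is the empty month-3 cell an extraction error?** In the same table, the row for "height, weight, blood pressure and HbA_1c" carries marks at 0, 3 and 6 months, so the columns were read correctly. {18a} also gives month 6 independently in prose.

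**Step 3: on-study harms record by attendance pattern**

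| Attendance | Hypoglycaemia if {22} is followed | Hypoglycaemia if Table 1 and {18a} are followed | Ketoacidosis, lactic acidosis (Table 1 and {18a}; not in {22}) | HbA1c used at month 6 ({20c}) |
|---|---|---|---|---|
| Months 3 and 6 | two reports | one report, six-month recall | recorded at month 6 | observed |
| Month 3, not month 6 | one report | none scheduled | none scheduled | month-3 value carried forward |
| Neither | none | none | none | baseline value carried forward |

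The second row is where the choice of schedule decides whether hypoglycaemia is recorded at all. For ketoacidosis and lactic acidosis, that row is empty whichever schedule is used.

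**Step 4: size of the group in the second row.** Inputs from {14}: 220 required, 20% loss, 264 in total.

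- Inflation as the article applies it: 220 × 1.20 = 264, which leaves room for 264 − 220 = 44 losses.
- 20% of those enrolled: 0.20 × 264 = 52.8, about 53.

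Both figures are total losses. Only those who attend month 3 and miss month 6 belong to the group, and the article does not give the timing of loss. If every loss comes before month 3 the group is empty. If every loss comes after month 3 it is about 44 to 53. The range is therefore 0 to about 44–53, and the documents support no point estimate within it.

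**The case against.** The best defence is that {22} is the section that governs harms and it expressly names month 3. {18a} says that on-study complications are recorded at month 6, but it does not forbid earlier registration. There could be two streams: adverse-event registration of hypoglycaemia at months 3 and 6, and a clinical-history form for acute complications at baseline and month 6. Table 1 has no adverse-event row, so its empty cell does not clearly cancel {22}. On that reading the fault is an omitted table entry, and no hypoglycaemia data are lost.

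This reading is possible, and it rightly makes the loss of hypoglycaemia data conditional on the forms following Table 1. It does not remove the need to reconcile. The article nowhere describes two streams. If they exist, a completer's hypoglycaemia is counted twice over different recall periods, with no rule for which count is reported.

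A reader might also infer that ketoacidosis and lactic acidosis will be missing from the harms report. The article does not say so. For completers these events are recorded at month 6 and stay in the dataset, and their tabulation may be set out in the full protocol or analysis plan. What stands is narrower: {22} does not count them as adverse events, and anyone who leaves before month 6 has no scheduled record of them.

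**Conclusion.** The inconsistency is real and certain on the text: {22} schedules hypoglycaemia at month 3, while Table 1 and {18a} do not. The restriction of adverse events to hypoglycaemia, when two more serious acute events are collected beside it, is equally plain.

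The consequence is conditional. Six-month recall, and the absence of a hypoglycaemia record for those who attend month 3 and miss month 6, arise only if the case forms follow Table 1 and {18a}. The gap for ketoacidosis and lactic acidosis in that same group exists under either schedule. The group numbers between 0 and about 44–53 of 264.

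Two stronger readings are not supported. It is not a three-way disagreement, because Table 1 and {18a} match. Nor will about 53 people lose their harms data: that figure is an upper bound on all losses, at an unstated time.

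Neither the primary outcome nor its analysis is affected. The matter should be corrected because harms data are thin by design and the remedy is cheap.

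**What to change.** 1. Give the same visits in {22}, Table 1 and {18a}. Add acute complications, including hypoglycaemia, at month 3 in Table 1 and {18a}, and state that the month-6 form then covers the time since month 3.
2. State which hypoglycaemia count is reported. If an adverse-event register and an acute-complications form both exist, say which is the source for the comparison between arms.
3. State that ketoacidosis and lactic acidosis are reported by arm as harms alongside hypoglycaemia.
4. The trial has been running since October 2021, so some participants may already have passed month 3. Report which schedule the forms followed, and how many participants attended month 3 but not month 6.

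Cost: one table mark, a few sentences, one repeat of an existing form at a visit participants already attend, and notification to the ethics committee under {25} if this is treated as an important modification. Sample size, treatment and the primary analysis do not change.

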## Interventions

### Intervention description {11a}

The Control group will undergo routine diabetes management: they will receive a standard portable glucose meter (Dnurse He pro wisdom; Beijing Dnurse Technology Ltd, Beijing, China) and blood glucose monitoring record book. The recommended timing and frequency of blood glucose monitoring will be explained to them according to national guidelines [9].

The Reminder group will receive the same materials as the Control group as well as a weekly telephone reminder to self-monitor blood glucose regularly. These reminders will be given by specially selected nursing undergraduates who have been trained in the rationale, interventions, and objectives of the study. Only nursing students who performed well on post-training testing are allowed to participate in the study. During the telephone call, students will ask participants whether they are self-monitoring regularly and, if not, what are the reasons.

The App group will receive a smart blood glucose meter (Dnurse SPUG mobile blood glucose uric acid tester; Beijing Dnurse Technology Ltd), and they will be led by a specially trainer researcher to download the Dnurse App 4.0.16 (dnurse.com/v2/app), designed to work smoothly with the smart blood glucose meter. The researcher will show the study participants how to open a personal account on the application and how to generate personalized diet and exercise programs, glucose control targets, and a blood glucose monitoring plan; how to access the food bank, disease information, and real-time blood glucose analysis and recommendations within the application; and how to set reminders to take medication and engage in other behaviors.

The App + Reminder group will receive the same materials and training as the App group, together with weekly telephone reminders like the Reminder group.

If members of the Control group and the Reminder group experience acute complications of diabetes, such as excessively high or low blood glucose, trial investigators will advise them to seek medical treatment as per standard procedures. If members of the App group and the App + Reminder group trigger a “critical value” alarm on the application, the customer service staff of the application’s manufacturer will call them by telephone and provide advice or information as per standard procedures. Both devices pass through ISO13485 and EU CE certifications.

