## Discussion

This trial aims to assess whether the smartphone application Dnurse can improve glycemic management and disease control in T2DM patients. Smartphone-based management and follow-up of diabetes is much less labor-intensive than direct follow-up by clinicians, and it can give individuals a sense of power and ownership of their condition, which may improve self-monitoring and treatment compliance [7, 16].

Despite the potential for smartphone applications to help people adopt healthier dietary and lifestyle behaviors [17], several studies suggest that they are not always effective. For example, a systematic review [18] found that only one of 11 studies assessing whether smartphone applications can improve T2DM self-management found a significant difference in HbA_1c_ related to application use, but none of seven studies assessing blood pressure found a significant difference, and only one of two studies assessing self-care found a significant difference. The investigators in those studies concluded that Apps had the potential to enhance diabetes management and glycemic control, but that further research was needed. The present trial will explore this potential using a rigorous, factorial design that will benchmark the application against routine care as well as telephone reminders. In addition, the trial will not exclude individuals with T2DM who are elderly or have diabetic eye diseases, which may make the findings of our study generalizable to a larger proportion of the global population with T2DM. Finally, our trial will substantially extend the literature on diabetes-related smartphone applications by examining a Chinese population, in contrast to the Western populations in most previous studies. China contains the largest number of smartphone users worldwide (nearly 1 billion), and the use of smartphone applications can be substantially higher than in the West [19].

In a survey in China, the Dnurse application was the most popular among T2DM patients and second most popular among individuals with type 1 diabetes [8]. It will be matched in the trial to a blood glucose meter from the same manufacturer, such that blood glucose data will be transmitted automatically to the application. This relieves the individual from the need of inputting data him- or herself, which may improve compliance with blood glucose monitoring [8].

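### Hypoglycaemia, the only event labelled adverse, is an ungraded participant-reported count, while detection aids differ by arm, so arm comparisons can reflect detection rather than risk

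*Protocol article*

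**What the plan says.** Adverse event reporting and harms {22} sets both the definition and the timing: "The adverse events in this study refer to hypoglycemia and will be registered at 3rd month and 6th month after the intervention". It then names the source: "And the participants inform the doctor of the number of hypoglycemia times during outpatient visits". The section separates neither severity nor symptoms, and it names no device record as a source.

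Intervention description {11a} equips the arms differently. Control and Reminder participants get a standard portable meter "and blood glucose monitoring record book". App and App + Reminder participants get a smart meter and an application with real-time glucose analysis. The Discussion says the two are paired "such that blood glucose data will be transmitted automatically to the application". Section {11a} continues: "If members of the App group and the App + Reminder group trigger a “critical value” alarm on the application", customer service staff of the "manufacturer will call them by telephone and provide advice or information as per standard procedures". In the other two arms the investigators advise participants who experience high or low glucose, and no alarm is described. The two Reminder arms also receive weekly calls prompting self-monitoring.

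Sections {17a} and {17b} make the trial open label, with only the HbA1c laboratory tester blinded. Objectives {7} asks whether the application changes compliance with monitoring, and Outcomes {12} makes monitoring frequency a secondary outcome.

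Table 1 and section {18a} also collect hypoglycaemia, as an acute complication, at baseline and then at month 6 only.

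**The concern.** A reported episode has to be noticed, recognised as hypoglycaemia, remembered and mentioned. The interventions act on the first three of these steps. A reading that is stored, analysed at once, flagged by an alarm and discussed on the telephone is more likely to be recognised and remembered than one in a paper book. If the application or the reminders increase testing, as the trial hopes, more low readings will be found at the same true rate. A distortion in the other direction is also possible: an App-arm participant whose alarm was dealt with by the manufacturer may not mention it to the doctor.

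With a single ungraded number per participant, these effects cannot be separated afterwards. Episodes that depend little on testing, such as those needing another person's help, are pooled with low readings that only a meter would reveal. A later analysis plan cannot recover a distinction that was never asked about.

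At stake is the reading of the one registered harm in a trial of tools meant to improve glycaemic control, in participants who may be taking oral hypoglycaemic drugs or insulin ({18a}). The primary outcome is not touched, since HbA1c is measured by a blinded laboratory.

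**Working it through.** The document gives no hypoglycaemia rate, detection probability or power for harms, so there is no stated figure to reproduce. The check is a comparison of sections, followed by an illustration on assumed values.

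**Sections side by side**

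| Step | Control | Reminder | App | App + Reminder | Source |
|---|---|---|---|---|---|
| Recording | meter and book | meter and book | automatic | automatic | {11a}, Discussion |
| Real-time analysis, alarm | none described | none described | yes | yes | {11a} |
| Call after alarm | none described | none described | manufacturer | manufacturer | {11a} |
| Weekly prompt to test | no | yes | no | yes | {11a} |
| Route into the count | participant tells doctor | same | same | same | {22} |

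Only the last row is equal. The rows above it decide whether there is an episode to tell.

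**Illustration**

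- *Inputs from the document:* 264 randomised in equal proportion ({14}, {8}), so 264 / 2 = 132 on each side of the App factor. With the 220 of the sample size calculation, 220 / 2 = 110.
- *Assumed inputs:* true risk of at least one episode p = 10%, 20% or 30%, equal on both sides, and a probability s that an affected participant is recorded. Section {22} registers a number of episodes; a yes/no version is used here for simplicity.
- *Observed risk* = p × s, so with equal true risks the observed ratio is s(App) / s(non-App).
- *Chance of a spurious significant excess* on the better-detected side, two-sided 5% test: Φ[(d − 1.96 × se0) / se1]. Here d is the observed difference, se0 the pooled standard error and se1 the unpooled one. Without bias this chance is 2.5%.

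Example with p = 20%, s = 0.90 against 0.60 and n = 132:

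- observed risks 0.18 and 0.12, d = 0.06, pooled risk 0.15
- se0 = √(0.15 × 0.85 × 2/132) = 0.0440
- se1 = √((0.18 × 0.82 + 0.12 × 0.88)/132) = 0.0438
- (0.06 − 1.96 × 0.0440) / 0.0438 ≈ −0.60, and Φ ≈ 0.28

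| s, App / non-App | Observed ratio | Spurious excess at p = 10 / 20 / 30%, n = 132 | Same, n = 110 |
|---|---|---|---|
| 0.70 / 0.70 | 1.00 | none beyond nominal | none beyond nominal |
| 0.80 / 0.70 | 1.14 | 5 / 7 / 8% | 5 / 6 / 8% |
| 0.90 / 0.60 | 1.50 | 15 / 28 / 42% | 13 / 24 / 36% |
| 0.90 / 0.50 | 1.80 | 25 / 47 / 67% | 21 / 40 / 59% |

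The bias can also hide a difference. At 0.90 against 0.60, a true ratio of 0.67 is seen as 0.67 × 1.5 ≈ 1.0. If detection were worse in the App arms (0.60 against 0.90), equal risks would be seen as 0.60 / 0.90 = 0.67, an apparent benefit.

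**Timing.** Section {22} registers hypoglycaemia at months 3 and 6. Table 1 and {18a} record it after baseline at month 6 only. These passages do not agree.

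**The case against.** The strongest answer is that {22} sets one reporting route for every arm and makes neither alarms nor application data the source of the count anywhere. That is right: unequal detection is an inference from {11a}, {22} and the Discussion, and the document does not state it. The inference still stands, because an identical last step does not equalise the steps before it.

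Hypoglycaemia is neither an objective nor a listed outcome, and the article plans no between-arm test of it. This also stands. The point is therefore limited to any comparison of the registered counts by arm, and no planned test is shown to be invalid.

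Monitoring frequency is asked of all participants at months 3 and 6. This is a real mitigation, and the fix uses it. It addresses testing intensity only, not alarms, calls or recall.

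The article is condensed, and a case definition or a transfer of alarm data may stand in the full protocol. So the absence of a glucose threshold is not counted here as a fault. What the article does state is the source and form of the count, and those are the subject of this point.

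Three stronger readings are tempting and unsupported:

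- *The App arms will show an excess.* The mechanisms pull both ways, and the document has no data to weigh them.
- *App-arm events will be lost to the manufacturer.* The participant triggers the alarm and receives the call, so can report it. Nor does the article say that a critical value means a low one.
- *The alarm log should be added to the adverse event count.* The log exists only in the App arms, so adding it would create the very asymmetry at issue.

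**Conclusion.** The point holds as a limited, inexpensive improvement to data collection. The single registered harm is an undifferentiated count reported to an unblinded doctor, in a trial whose interventions change how readily episodes are found. A difference by arm, or the lack of one, could not be read as a difference in true risk.

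The size is unknown. The ratios of 1.14 to 1.80 above, and the corresponding false-positive chances, rest wholly on assumed risks and detection probabilities. They show what modest and large imbalances would do, not what this trial will see. The conclusion rests on two premises: that automatic capture, alarms, calls and prompts affect recognition or recall, and that the counts will be compared by arm at all. The disagreement over visit timing is a separate inconsistency that needs no assumption.

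**What to change.** In {22}:

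1. At the existing month 3 and month 6 visits, put the same fixed question to all four arms. It should count separately (a) episodes needing another person's help, (b) other symptomatic episodes and (c) low readings without symptoms. Use (a) and (b) for any between-arm safety statement. This reduces the detection problem without removing it: (a) depends least on testing, while (b) can still be affected by alarms and open-label recall.
2. Tabulate device-detected low readings, and App-arm critical-value alarms or calls, separately and descriptively. Never add them to the between-arm count. In the non-App arms such readings may come only from the record book, since the article does not say that the standard meter stores them.
3. Present non-severe counts beside the monitoring frequency already collected at months 3 and 6.
4. Reconcile the months 3 and 6 of {22} with the month 6 only of Table 1 and {18a}.

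This concerns data collection only and leaves care and advice to participants as they are. The cost is slight extra data entry at visits that already take place. The trial began in October 2021, so visits already completed cannot be re-asked in the same way. Data collected before and after the change should be shown separately.
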